## Abstract

**Background:**

Managing therapy-related side-effects and improving health-related quality of life in patients with colorectal cancer is still challenging. The need for an effective management of adverse events and unmet supportive care needs have been widely discussed. In the past decade, interventions by nursing staff gained more and more importance. Evidence suggests that a majority of patients even in early stages of the disease experience substantial impairments potentially resulting in diminished therapy adherence as well as impaired quality of life. However, evidence for the effectiveness of nurse-led interventions on symptom management and quality of life is still very limited. This especially applies to care transitions between different inpatient and outpatient health care providers throughout the course of treatment and aftercare.

**Methods/Design:**

Supportive Cancer Care Networkers (SCAN) is a prospective randomized controlled trial conducted in eight large and middle-sized German cancer centers and municipal hospitals. The target population is adults with colorectal cancer UICC I-III after initial R-0 resection scheduled for adjuvant chemotherapy or guideline-based aftercare only. 370 patients will be randomly assigned to either intervention or control group. Patients in the intervention group will receive an additional support by specialized oncology nurses for eight weeks after discharge from hospital by telephone, consisting of symptom monitoring, counselling on self-assessment and self-management and dealing with individual resources for coping and psychosocial well-being. The primary endpoint will be health-related quality of life (HRQoL) at eight weeks after discharge from the initial treating hospital.

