## Methods/Design

### Study design

SCAN is a prospective randomized controlled multi-center trial in adult patients with colorectal cancer (International Classification of Diseases, ICD-10 C18-20) in Union internationale contre le cancer (UICC) stage I-III. The study is conducted in the surgical wards of eight large and middle-sized cancer centers and general hospitals in Saxony-Anhalt and Saxony, Germany.

Patients randomly assigned to the intervention arm receive additional support by specially trained oncology nurses for eight weeks after discharge from hospital following surgical therapy. Allocation to either intervention or control group is performed with equal ratio. The following amendments were submitted to the local ethics committee and approved on June 4^th^ 2013:Expansion of eligibility criteria to UICC stage I andChange of the primary outcome from adjuvant chemotherapy utilization to HRQoL.

Both amendments are causally linked to one another. Prior to the amendment only patients with UICC stage II & III were eligible for trial inclusion because of the actual medical guideline for the treatment of colorectal cancer. According to this guideline, adjuvant chemotherapy is indicated in patients with UICC stage II and more advanced tumor states only. Due to upcoming effects of the establishment of the preventive colonoscopy as a standard benefit of the German statutory health insurance a noticeable shift regarding tumor stages is obvious. Studies, which were published after approval of the study by the sponsor show that colorectal cancer, despite of the low participation rate of the healthy general population is detected significantly more often in early stages (UICC I) [36, 37] than previous reference data suggested. Nevertheless, this positive effect leads to a significant reduction of the patients eligible for the study. With the additional inclusion of patients in the UICC stage I a rise of the case number of approx. 40 % could be achieved. At the same time, patients in UICC I are not indicated to adjuvant chemotherapy. As a result, widening the eligibility criteria had to be accompanied by changing the primary outcome. Since HRQoL had been defined as a central secondary outcome, the primary outcome was replaced by a former secondary one without changing elements or procedures of the intervention itself.

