### Sample size

For sample size calculation the portion of the patients who reach a clinically relevant improvement of the global health-related quality of life (HRQoL) within 8 weeks after discharge from hospital is chosen. The sample size calculation is based on an expected response difference of 15% points in the subscale *“global health status”*/QoL of QLQ-C30 EORTC between the intervention and the standard treatment 8 weeks after the clinic dismissal after surgical therapy. Own reference data [30] show a response of 48 % in standard treatment, so that in the intervention group responses of 63 % are expected. To be able to detect a relevant effect of the intervention with a rise of the responses by 15% points with 80 % power, *n* = 370 patients (*n* = 185 patients per study arm) are needed. Including a dropout rate of approx. 10 %, *n* = 406 patients (*n* = 203 per study arm) will be recruited.

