### Statistics

#### Primary endpoint analysis

The analysis of the primary outcome will obey to the intention-to-treat principle using generalized linear regression modelling and reported as relative risk with its according 95 % confidence interval. The model will be adjusted for cancer site, tumor stage, cancer therapy, ECOG performance status, age, sex and eventual previous neoadjuvant radiation therapies.

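### The abstract gives 370 as the number randomised, but the sample-size section needs 370 for analysis and recruits 406

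*Protocol article*

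**What the plan says.** Two places in the protocol article give a number of patients.

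- **Abstract, Methods/Design:** "370 patients will be randomly assigned to either intervention or control group".
- **Methods/Design, Sample size:** the inputs are "Own reference data [30] show a response of 48 % in standard treatment" and "in the intervention group responses of 63 % are expected", and the aim is to detect an effect "with a rise of the responses by 15% points with 80 % power". The result is 370 patients, 185 per arm. The section then adds an allowance ("Including a dropout rate of approx". 10 %) and arrives at 406 patients to be recruited, 203 per study arm.

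Three other statements bear on the point. The Study design section says "Allocation to either intervention or control group is performed with equal ratio". The Intervention section says that patients who meet the criteria and sign consent are randomised. The Primary endpoint analysis section plans a covariate-adjusted generalised linear model, with the result "reported as relative risk with its according 95 % confidence interval". The Sample size section itself states no significance level, no sidedness and no test.

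**The concern.** The same figure, 370, does two different jobs. In the Sample size section it is the number that must be available for analysis. In the abstract it is the number allocated. Both cannot hold if any dropout is expected, and the plan expects about 10%.

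A reader who takes the target from the abstract would understand that randomisation ends 36 patients earlier than the Sample size section provides for. The dropout allowance would then vanish and the stated 80% power would not be reached. The abstract is also the part of the article most readily taken as the trial's headline size.

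**Working it through.** **Inputs.** From the Sample size section: control response 0.48, intervention response 0.63, power 80%, 370 needed, 406 recruited, dropout about 10%. From Study design: 1:1 allocation. Assumed, because it is not stated: two-sided alpha of 0.05, which fits the 95% confidence interval planned for the primary analysis.

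**Step 1. Reproduce the plan's figure.** With mean proportion 0.555 and difference 0.15:

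- √(2 × 0.555 × 0.445) = 0.7028
- √(0.48 × 0.52 + 0.63 × 0.37) = 0.6948
- n per arm, uncorrected = [(1.960 × 0.7028 + 0.8416 × 0.6948) / 0.15]² = 171.1, so 172 (344 in total)
- n per arm, continuity-corrected = (171.1 / 4) × [1 + √(1 + 4 / (171.1 × 0.15))]² = 184.2, so 185 (370 in total)

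The corrected formula matches the plan exactly. The other variants do not: unpooled variance gives 169 per arm, arcsine 171, and one-sided 5% gives 135 (148 with correction). The figure of 370 is therefore sound as a number for analysis. The match supports the assumption of two-sided 5% with continuity correction, but does not prove it.

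**Step 2. What each target leaves after a 10% loss.**

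- 370 × 0.9 = 333, or 166.5 per arm
- 406 × 0.9 = 365.4, or 182.7 per arm (about 183)

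**Step 3. Power at those sizes.** Power = Φ[(d√n − 1.960 × 0.7028) / 0.6948], where d = 0.15 uncorrected and d = 0.15 − 1/n with the continuity correction. For example, at n = 166.5 the corrected d is 0.1440, d√n = 1.858, and Φ(0.692) = 0.755.

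| Per arm analysed | Arises from | Corrected | Fisher exact | Uncorrected |
|---|---|---|---|---|
| 185 | plan's requirement | 80.2% | 80.9% | 83.0% |
| 183 | 406 less 10%, rounded | 79.7% | 80.1% | 82.6% |
| 166.5 | 370 less 10% | 75.5% | 76.3% (166) to 76.8% (167) | 78.9% |

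At the unrounded 182.7 per arm the corrected and uncorrected values are 0.7965 and 0.8253, which makes no practical difference.

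**Step 4. The size of the dropout allowance.** The largest dropout at which 406 still leaves 370 is 1 − 370/406 = 8.9%. Inflating by division gives 185 / 0.9 = 205.6, so 206 per arm and 412 in total. The printed 203 is close to 185 × 1.1 = 203.5 rounded down; the 36 added patients are 36/370 = 9.7% of the base. The article does not show which calculation was used. The gap between 406 and 412 is six patients, or 1.5%.

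**The case against.** **Recruited is not the same as randomised.** One could suppose that 406 are recruited and 370 of them are allocated. The text does not bear this out. The 406 is given as 203 per study arm, and a patient has an arm only after allocation. The Intervention section goes straight from eligibility and consent to randomisation, with no loss in between. The primary endpoint is measured 8 weeks after discharge, so the losses that a dropout allowance covers would fall largely after allocation.

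**The power loss is conditional, and its size depends on the test.** This stands. The dedicated section says that 406 will be recruited, and nothing in the methods makes 370 a stopping number. The likeliest explanation is that the abstract picked up the figure before dropout. The continuity correction is inferred only from the match with 185, whereas the planned analysis is an adjusted regression. Without the correction, even 370 less 10% falls only about one point short of 80%. Both ends of the range should therefore be shown.

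**A stronger reading a reader might infer: that even 406 fails to deliver 80% power.** It is true that 406 less exactly 10% leaves about 365, not 370. But the plan gives dropout only as approximate, an allowance of 8.9% is a fair reading of that, and power at 183 per arm lies between 79.7% and 82.6%. The documents do not support a claim that 406 is too few.

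**Conclusion.** The contradiction is real: the abstract and the Sample size section give randomisation targets of 370 and 406, and they must be reconciled. This rests on the printed text alone and needs no assumption.

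Its possible consequence is moderate and conditional. If 370 were the number randomised and 10% were lost, about 333 would be analysed, with power of 75.5% (continuity-corrected) to 78.9% (uncorrected) instead of 80%. That range assumes a two-sided 5% level, the plan's own response rates and an unadjusted comparison of two proportions.

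The point does not show that the trial as set out in its Sample size section is underpowered. The requirement of 370 reproduces exactly. The dropout inflation is a few patients light by strict arithmetic, which is a minor slip with no practical effect on power.

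**What to change.** Change the abstract to match the Sample size section, for example: *406 patients will be randomised (203 per arm); 370 are needed for analysis.* This avoids saying that 406 will yield 370 at a 10% loss, which the arithmetic does not support.

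In the Sample size section, state the dropout allowance as about 9%, which is what 406 provides for. It would help to name the significance level, sidedness and test in the same sentence, so that 185 per arm can be checked directly.

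The cost is wording only. Moving to 412 would add six patients and is not needed.

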**Discussion:**

The presented SCAN trial is to provide information that will be useful to advance our understanding of complex interdependencies between symptom severity, supportive care needs, functioning and the risk for diminished HRQoL. Most importantly, these patient-reported outcomes are not fully implemented in today’s clinical routine practice potentially resulting in therapy cessations and lower chemotherapy treatment rates for colorectal cancer especially in older patients.

**Trial registration:**

ClinicalTrials.gov Identifier NCT01651832.

## Background

### Incidence and prevalence

Colorectal cancer (CRC) is the second most frequent malignant disease in Germany with 62,430 newly diagnosed cases in 2010, 5-year prevalence of 214,300 and with more than 25,000 cases persistently the second most frequent cause of cancer death [1]. During the past decade, 5-year relative survival from colorectal cancer increased to 65 %. Despite of effective primary prevention, prevalence will continue to grow at over 3 % per year [2]. Thus, a growing number of survivors of colorectal cancer are likely to experience unmet supportive care needs (SCN) during the course of treatment to a different extent as well [3]. We are now questioning the possibilities of covering those supportive needs properly without exceeding personnel and financial resources.

### Unmet supportive needs

Recently published studies revealed a significant share of patients whose supportive needs are not covered entirely within routine care practice today [4]. Unmet supportive needs in turn have been proven to be significantly associated with diminished health-related quality of life (HRQoL). Such unmet supportive needs can refer to either physical or psychological symptoms as well as accessibility of health care or social welfare benefits. Meeting these needs is likely to improve the patients’ quality of life by lowering symptom severity and psychological distress and might prevent dissatisfaction with health care [5–8].

But, while the assessment of cancer or therapy-related symptoms is more and more integrated into routine supportive therapy, the assessment of SCN still lacks a systematic implementation [9–11]. An especially critical phase in the course of treatment for not addressing the patients’ supportive needs sufficiently is the transition from in-patient primary therapy to out-patient aftercare [12]. Especially in more than 30 % of elderly patients (65+) chemotherapies are discontinued within 1–4 months due to persistently high levels of symptoms and functional impairments, leading to significantly diminished survival [13]. Therefore, national and international guidelines on the treatment of colorectal cancer recommend optimizing treatment of side-effects and cancer-related symptoms seamlessly [14–16]. Hence, a systematic monitoring is necessary for the treatment of symptoms and impairments [16].

Recent reference data from the QUASAR2-trial [17] proved that up to 30 % of patients suffer from substantial therapy-induced symptoms during active therapy. Depending on the regime, common toxicities in patients with colorectal cancer are diarrhea, nausea and vomiting, mucositis/stomatitis, myelosuppression, and hand-foot syndrome. This may lead to avoidable impairments in HRQoL as it is often found in patients with colorectal cancer [18–20]. Moreover, the necessity for follow-up treatment can last for years after initial diagnosis and treatment as a recent analysis in long-term survivors in the US with leukemia, bladder, and colorectal cancer showed [21]. And even without being indicated to adjuvant chemotherapy, patients in early tumor stages usually state increased psychosocial and medical supportive needs, especially after surgery [22].

### Nursing interventions to address SCN

In the past, nursing interventions for the improvement of access to the care for cancer patients, for the support in managing therapy-related side-effects, for the improvement of therapy compliance and care continuity [23] as well as for the improved treatment management have gained importance [10, 24–26]. The early detection of therapy-related symptoms and functional restrictions by nursing staff can contribute particularly to the improvement of outpatient aftercare and sustain patients’ motivation for therapy compliance [17]. Additional information on patients’ medical condition using patient-reported outcomes (PROs) can contribute to support professionals involved in clinical decision making [25, 27].

Problem for cancer and other chronic diseases is the fact that the medical condition as well as the resulting supportive needs change during the course of the disease and are hardly predictable [10]. That is why the routine collection of relevant disease parameters and supportive care need measures within integrated care concepts is essential during the entire course of the treatment. We were able to show that due to nursing interventions symptom-related supportive care needs concerning disease- or treatment-related side-effects (nausea, vomiting, pain, fatigue, malnutrition) can partially be addressed beyond inpatient treatment by conveying self-management abilities and an attitude change in patients regarding cancer [28–30].

In general, there is still a lack of nursing interventions that cover unmet SCN of all different aspects during primary therapy and care transition. Random models have been evaluated within clinical trials, such as e.g. patient navigators, either based on nursing staff or lay persons. Recently, special attention was paid e.g., on such guidance throughout the course of treatment in a study by Wagner et al. [31]. The *Nurse Navigator* program providing additional support regarding care access, distress and fatigue assessment by telephone for 4 months was compared to usual care. While patients in the *Nurse Navigator* group stated improved experience and reduced problems in care access, the overall HRQoL was not affected significantly. These findings might not be standing in contrast to prior findings. As a study on the newly developed Comprehensive Concerns Assessment Tool and the European Organization for Research and Treatment of Cancer (EORTC) showed, the most important factors were related to self-management abilities, psychological symptoms and medical information rather than the usual suspects, i.e. pain or gastrointestinal symptoms [32]. Furthermore, continuous access to qualified health care providers and other resources for the management of long-term debilitating symptoms is essential from the patient’s view even for years after the initial diagnosis and treatment [33]. There is preliminary evidence for the feasibility and acceptance of an electronic monitoring of symptoms that could be useful for clinical decision making, too [34]. Thus, it is to be assumed that prior standardized interventions as mentioned above failed to address the entire variety of changing unmet SCN in differing phases of the care process sufficiently, leading to a possible mismatch between the patient’s current condition and the support provided. Following the state of research, in these subjects a personalized approach as proposed in this paper, can take on an important role. Moreover, our approach is likely to add in-depth information on interdependencies between different domains of SCN in order to facilitate the promotion of HRQoL effectively.

### Objectives

The main purpose of this study is to increase the proportion of patients achieving a clinical relevant improvement of their health-related quality of life of 10pts. [35] by 15 % compared to usual care. Secondary objectives are toDetermine the prevalence, time of occurrence and severity of unmet SCN,Analyze effective elements of nurse-led patient counselling on patient self-management, self-assessment and knowledge,Identify individual resources that medical professionals can strengthen and utilize to build up the patient’s autonomy and coping abilities andDetermine the effect of a supportive nurse-led intervention on disease-free survival 8 months after surgery.

## Methods/Design

### Study design

SCAN is a prospective randomized controlled multi-center trial in adult patients with colorectal cancer (International Classification of Diseases, ICD-10 C18-20) in Union internationale contre le cancer (UICC) stage I-III. The study is conducted in the surgical wards of eight large and middle-sized cancer centers and general hospitals in Saxony-Anhalt and Saxony, Germany.

Patients randomly assigned to the intervention arm receive additional support by specially trained oncology nurses for eight weeks after discharge from hospital following surgical therapy. Allocation to either intervention or control group is performed with equal ratio. The following amendments were submitted to the local ethics committee and approved on June 4^th^ 2013:Expansion of eligibility criteria to UICC stage I andChange of the primary outcome from adjuvant chemotherapy utilization to HRQoL.

Both amendments are causally linked to one another. Prior to the amendment only patients with UICC stage II & III were eligible for trial inclusion because of the actual medical guideline for the treatment of colorectal cancer. According to this guideline, adjuvant chemotherapy is indicated in patients with UICC stage II and more advanced tumor states only. Due to upcoming effects of the establishment of the preventive colonoscopy as a standard benefit of the German statutory health insurance a noticeable shift regarding tumor stages is obvious. Studies, which were published after approval of the study by the sponsor show that colorectal cancer, despite of the low participation rate of the healthy general population is detected significantly more often in early stages (UICC I) [36, 37] than previous reference data suggested. Nevertheless, this positive effect leads to a significant reduction of the patients eligible for the study. With the additional inclusion of patients in the UICC stage I a rise of the case number of approx. 40 % could be achieved. At the same time, patients in UICC I are not indicated to adjuvant chemotherapy. As a result, widening the eligibility criteria had to be accompanied by changing the primary outcome. Since HRQoL had been defined as a central secondary outcome, the primary outcome was replaced by a former secondary one without changing elements or procedures of the intervention itself.

### Study population

The target population is adult patients with colorectal cancer (International Classification of Diseases, ICD-10 C18-C20, UICC I-III) in curative therapy conditions. Eligible patients will be identified after surgery by hospital physicians through histological and pathological findings. Eligible patients expressing interest in taking part in the study will be contacted by a specially trained oncology nurse and an initial appointment will be scheduled. Fully informed written consent will be obtained before collecting any data or providing counseling.

### Inclusion criteria

Being treated surgically at one of the participating study centers for colorectal cancer (R0)Age 18–85 years.ECOG performance status 0–2Prospective further life expectancy of >3 months.Living in Saxony-Anhalt or Saxony.Ability to participate in regular follow-up intervals as determined in the medical guidelineInformed written consent must be obtained according to ICH/EU GCP, before trial inclusion.

